**Subgroup analyses**

No subgroup analyses will be performed.

**Other data summaries**

- Number of participants on both treatment arms who began taking orlistat during follow-up
- Compare weight change at 12 months in participants who received orlistat during follow-up vs. those who did not
- Summary measures for the feedback questionnaire form (mean and SD, number and percent) in both treatment arms for Q1, Q2, and Q4

1. **Figures**

**Participant flow**

Participant throughput will be summarized in a CONSORT diagram (see figure 1).

| **Figure 1: Consort Diagram** | | | | | | | | | | | |
| --- | --- | --- | --- | --- | --- | --- | --- | --- | --- | --- | --- |
|  |  |  |  | Screened for eligibility  (N= XX) | | | |  |  |  |  |
|  |  |  |  |  |  |  |  |  |  |  |  |
|  |  |  |  |  |  |  |  | Excluded (N=XX)   - Not eligible (N=XX) - Declined to participate (N=XX) | | | |
|  |  |  |  |  |  |  |  |  |  |  |  |
|  |  |  |  | Randomised (N=XX) | | | |  |  |  |  |
|  |  |  |  |  |  |  |  |  |  |  |  |
| Allocated to Intervention (WAP) (N=XX)   - Began receiving treatment (N=XX) - Completed at least 50% of sessions (N=XX) | | | |  |  |  |  | Allocated to Control (nurse advice) (N=XX)   - Began receiving treatment (N=XX) - Completed at least 50% of sessions (N=XX) | | | |
|  |  |  |  |  |  |  |  |  |  |  |  |
| Attended 8-week follow-up (N=XX) | | | |  |  |  |  | Attended 8-week follow-up (N=XX) | | | |
|  |  |  |  |  |  |  |  |  |  |  |  |
| Attended 6-month follow-up (N=XX) | | | |  |  |  |  | Attended 6-month follow-up (N=XX) | | | |
|  |  |  |  |  |  |  |  |  |  |  |  |
| Attended 12-month follow-up (N=XX)   - Dropped out prior to the end of the study (N=XX) | | | |  |  |  |  | Attended 12-month follow-up (N=XX)   - Dropped out prior to the end of the study (N=XX) | | | |
|  |  |  |  |  |  |  |  |  |  |  |  |
| - Patients included in the analysis for the primary outcome (N=XX) | | | |  |  |  |  | - Patients included in the analysis for the primary outcome (N=XX) | | | |
|  |  |  |  |  |  |  |  |  |  |  |  |

**Other figures**

For certain outcomes, we will produce two graphs. The first graph will show the mean outcome within each treatment group (i.e. the mean outcome in the intervention arm, and the mean outcome in the control arm) at each time-point of follow-up. The mean outcome at each time point will be presented with a 95% confidence interval. The second graph will show the estimated treatment effect (with a 95% CI) at each time point.

These graphs will be produced for the following outcomes:

- Change in weight at 1, 2, 6, and 12 months
- Change in BMI at 1, 2, 6, and 12 months
- Change in waist circumference at 2, 6, and 12 months
- Change in systolic blood pressure at 2, 6, and 12 months

1. **Tables**

**Table 1 - Baseline measurements**

|  | Usual care (n=…) | WAP (n=…) |
| --- | --- | --- |
| Weight (kg) – mean (SD) |  |  |
| BMI – mean (SD) |  |  |
| Waist circumference – mean (SD) |  |  |
| Systolic blood pressure – mean (SD) |  |  |
| Diastolic blood pressure – mean (SD) |  |  |
| Age (years) – mean (SD) |  |  |
| Female – no. (%) |  |  |
| Food Craving Inventory score – mean (SD) |  |  |
| Frequency domain |  |  |
| Strength domain |  |  |
| Food Knowledge Assessment Questionnaire score – mean (SD) |  |  |
| Three Factor Eating Questionnaire score – mean (SD) |  |  |
| Cognitive Restraint domain |  |  |
| Uncontrolled Eating domain |  |  |
| Emotional Eating domain |  |  |
| International Physical Activity Questionnaire – mean (SD) |  |  |
| MET-minutes/week domain |  |  |
| Sitting domain |  |  |
| Centre – no. (%) |  |  |
| Lawson |  |  |
| Barkantine |  |  |
| Marital status – no. (%) |  |  |
| Single |  |  |
| Separated or divorced |  |  |
| Married or living with partner |  |  |
| Other |  |  |
| Ethnicity – no. (%) |  |  |
| White British |  |  |
| White other |  |  |
| Black |  |  |
| Asian |  |  |
| Mixed |  |  |
| Other |  |  |
| Educational qualification – no. (%) |  |  |
| None |  |  |
| GCSE or equivalent |  |  |
| A-Level or equivalent |  |  |
| Degree or equivalent |  |  |
| Other |  |  |
| Employment status – no. (%) |  |  |
| In paid employment |  |  |
| Unemployed |  |  |
| Looking after the home |  |  |
| Retired |  |  |
| Full time student |  |  |
| Other |  |  |
| Entitled to free prescriptions – no. (%) |  |  |
| Smoking status – no. (%) |  |  |
| Smoker |  |  |
| Non-smoker |  |  |
| Units of alcohol consumed per week – mean (SD) |  |  |
| Family history of being overweight or obese – no. (%) |  |  |
| Mother |  |  |
| Father |  |  |
| Themselves |  |  |
| Number of previous attempts at weight loss – median (IQR) |  |  |
| Greatest previous amount of weight loss – median (IQR) |  |  |

**Table 2 – Characteristics of intervention groups and patient adherence**

|  | Usual care (n=…) | WAP (n=…) |
| --- | --- | --- |
| Number of intervention groups or nurses (usual care) |  |  |
| Number of participants per group – median (IQR) |  |  |
| Number of sessions attended per participant – median (IQR) |  |  |
| Attended more than half the sessions – no. (%) |  |  |

**Table 3 – Number (%) of participants included in the analysis for each outcome**

|  | Usual care (n=…) | WAP (n=…) |
| --- | --- | --- |
| Change in weight |  |  |
| Change in BMI |  |  |
| Change in waist circumference |  |  |
| Change in systolic blood pressure |  |  |
| Change in diastolic blood pressure |  |  |
| Food Craving Inventory score |  |  |
| Frequency domain |  |  |
| Strength domain |  |  |
| Food Knowledge Assessment Questionnaire score |  |  |
| Three Factor Eating Questionnaire score |  |  |
| Cognitive Restraint domain |  |  |
| Uncontrolled Eating domain |  |  |
| Emotional Eating domain |  |  |
| International Physical Activity Questionnaire |  |  |
| MET-minutes/week domain |  |  |
| Sitting domain |  |  |
| Participants losing 5% of their body weight |  |  |
| Participants losing 10% of their body weight |  |  |

**Table 4 – Results for primary and secondary outcomes**

|  | **Usual care (n=…)** | **WAP (n=…)** | **Treatment effect* (95% CI)** | **P-value** |
| --- | --- | --- | --- | --- |
| Change in weight (kg) – mean (SD) |  |  |  |  |
| 1 month |  |  |  |  |
| 2 months |  |  |  |  |
| 6 months |  |  |  |  |
| 12 months |  |  |  |  |
| Change in BMI – mean (SD) |  |  |  |  |
| 1 month |  |  |  |  |
| 2 months |  |  |  |  |
| 6 months |  |  |  |  |
| 12 months |  |  |  |  |
| Change in waist circumference (cm) – mean (SD) |  |  |  |  |
| 2 months |  |  |  |  |
| 6 months |  |  |  |  |
| 12 months |  |  |  |  |
| Change in systolic blood pressure – mean (SD) |  |  |  |  |
| 2 months |  |  |  |  |
| 6 months |  |  |  |  |
| 12 months |  |  |  |  |
| Change in diastolic blood pressure – mean (SD) |  |  |  |  |
| 2 months |  |  |  |  |
| 6 months |  |  |  |  |
| 12 months |  |  |  |  |
| Change in Food Craving Inventory score (Frequency domain) – mean (SD) |  |  |  |  |
| 1 month |  |  |  |  |
| 2 months |  |  |  |  |
| 6 months |  |  |  |  |
| 12 months |  |  |  |  |
| Change in Food Craving Inventory score (Strength domain) – mean (SD) |  |  |  |  |
| 1 month |  |  |  |  |
| 2 months |  |  |  |  |
| 6 months |  |  |  |  |
| 12 months |  |  |  |  |
| Change in Food Knowledge Assessment Questionnaire score – mean (SD) |  |  |  |  |
| 2 months |  |  |  |  |
| 6 months |  |  |  |  |
| 12 months |  |  |  |  |
| Change in Three Factor Eating Questionnaire score (Cognitive Restraint domain) – mean (SD) |  |  |  |  |
| 2 months |  |  |  |  |
| 6 months |  |  |  |  |
| 12 months |  |  |  |  |
| Change in Three Factor Eating Questionnaire score (Uncontrolled Eating domain) – mean (SD) |  |  |  |  |
| 2 months |  |  |  |  |
| 6 months |  |  |  |  |
| 12 months |  |  |  |  |
| Change in Three Factor Eating Questionnaire score (Emotional Eating domain) – mean (SD) |  |  |  |  |
| 2 months |  |  |  |  |
| 6 months |  |  |  |  |
| 12 months |  |  |  |  |
| Change in International Physical Activity Questionnaire (MET-minutes/week domain) – mean (SD) |  |  |  |  |
| 2 months |  |  |  |  |
| 6 months |  |  |  |  |
| 12 months |  |  |  |  |
| Change in International Physical Activity Questionnaire (Sitting domain) – mean (SD) |  |  |  |  |
| 2 months |  |  |  |  |
| 6 months |  |  |  |  |
| 12 months |  |  |  |  |
| Participants losing 5% of their body weight – no. (%) |  |  |  |  |
| 2 months |  |  |  |  |
| 6 months |  |  |  |  |
| 12 months |  |  |  |  |
| Participants losing 10% of their body weight – no. (%) |  |  |  |  |
| 2 months |  |  |  |  |
| 6 months |  |  |  |  |
| 12 months |  |  |  |  |

*Treatment effects are presented as a difference in means (estimated from a mixed-effects regression model) between the two groups (WAP vs. control) for all outcomes apart for the number of participants who lost 5% or 10% of their body weight, where the treatment effect is presented as an odds ratio.

**Table 5 – ICC values for group or nurse at 6 and 12 months**

|  | 6 months | 12 months |
| --- | --- | --- |
| Change in weight |  |  |
| Change in BMI |  |  |
| Change in waist circumference |  |  |
| Change in systolic blood pressure |  |  |
| Change in diastolic blood pressure |  |  |
| Food Craving Inventory score |  |  |
| Frequency domain |  |  |
| Strength domain |  |  |
| Food Knowledge Assessment Questionnaire score |  |  |
| Three Factor Eating Questionnaire score |  |  |
| Cognitive Restraint domain |  |  |
| Uncontrolled Eating domain |  |  |
| Emotional Eating domain |  |  |
| International Physical Activity Questionnaire |  |  |
| MET-minutes/week domain |  |  |
| Sitting domain |  |  |
| Participants losing 5% of their body weight |  |  |
| Participants losing 10% of their body weight |  |  |

**Table 6 – No. (%) of participants in the WAP group using different process measures at each session**

| Process measure | S1 (n=…) | S2 (n=…) | S3 (n=…) | S4 (n=…) | S5 (n=…) | S6 (n=…) | S7 (n=…) | S8 (n=…) |
| --- | --- | --- | --- | --- | --- | --- | --- | --- |
| Pedometer use | No. (%) | No. (%) | No. (%) | No. (%) | No. (%) | No. (%) | No. (%) | No. (%) |
| TV/screen time use | No. (%) | No. (%) | - | - | - | - | - | - |
| Food diary use | No. (%) | - | - | - | - | - | - | - |
| Counted calories | - | No. (%) | - | - | - | - | - | - |
| 5/day | - | - | No. (%) | No. (%) | No. (%) | No. (%) | No. (%) | No. (%) |
| Exercise | - | - | - | No. (%) | No. (%) | No. (%) | No. (%) | No. (%) |
| No junk | - | - | - | - | No. (%) | No. (%) | No. (%) | No. (%) |
| Scales | - | - | - | - | No. (%) | No. (%) | No. (%) | No. (%) |
| Removed triggers | - | - | - | - | - | - | No. (%) | - |

1. **REFERENCES**

**Appendix 1**

***Timing of data collection***

| **Source of data** | **Data collected** |
| --- | --- |
| Baseline questionnaire | Age  Sex  Marital status  Ethnicity  Educational qualification  Employment status  Entitlement to free prescriptions  Smoking status  Alcohol Consumption  Eating Habits  Weight Loss history  Concurrent illnesses/ medications |
| CRF – screening session | Weight (kg)  Height (cm)  BMI  Eligibility checked against inclusion criteria |
| CFR – randomisation session | Weight (kg)  Waist circumference (cm)  Blood pressure  MPSS  Motivation scale  Use of other weight loss methods |
| CRF – control group treatment sessions | Weight (kg)  Waist circumference (cm) (Session 4 only)  Blood pressure (Session 4 only)  MPSS  Motivation scale (Session 1 only)  Use of other weight loss methods  AEs |
| CRF – intervention group treatment sessions | Weight (kg)  Waist circumference (cm) (Session 8 only)  Blood pressure (Session 8 only)  MPSS  Motivation scale (Session 1 only)  Use of other weight loss methods  AEs |
| Task cards (intervention group only) | Pedometer readings (reported and actual)  Step target  Screen time  Completion of food diary  Calorie counting  5/day  Exercise  ‘Said no’ to unnecessary food  Self monitoring on weighing scales |
| CRF – 6 month follow-up | Weight (kg)  Waist circumference (cm)  Blood pressure  Concurrent illness/medications  MPSS  Use of other weight loss methods  AEs |
| CRF – 12 month follow-up | Weight (kg)  Waist circumference (cm)  Blood pressure  Concurrent illness/medications  MPSS  Use of other weight loss methods  AEs |

**Appendix 2**

***Scoring of questionnaires***

**Food Knowledge Assessment score**

The Food Knowledge Assessment score is scored on an 11 point scale (range 0-10), with higher scores indicating more knowledge. It contains 10 questions, and each question is score either 0 or 1. The overall score is calculated by summing the scores of the individual questions.

The scores for the individual questions is shown in the table below. Each question has four possible answers (a, b, c, d); the table indicates which of the four answers results in a score of 1 (all other answers result in a score of 0).

|  | Score=1 if answer is |
| --- | --- |
| Q1 | A |
| Q2 | A |
| Q3 | C |
| Q4 | B |
| Q5 | D |
| Q6 | B |
| Q7 | C |
| Q8 | B |
| Q9 | B |
| Q10 | A |

**Food Craving Inventory score**

Each of the five food types (fatty foods, carbohydrates and starches, sweet foods, savoury snacks, and fruit) is assigned a score from 0 to 5 on both frequency and urge of craving. The frequency domain is then calculated by summing the scores of the individual questions related to frequency; the strength domain is calculated in a similar manner. The overall scores from both domains range from 0 to 25, with higher scores indicating more frequent or stronger urges.

**International Physical Activity Questionnaire**

***MET-minutes/week domain***

This score represents the total MET-minutes/week, and is expressed on a continuous scale with a minimum score of 0. It is calculated as:

MET-minutes/week = 3.3*(walking intensity minutes)*(walking intensity days) +

4.0* (moderate intensity minutes)*(moderate intensity days) +

8.0* (vigorous intensity minutes)*( vigorous intensity days)

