**Outcome measures**

Primary outcomes

The primary outcome measure is the change in weight (in kg) at 12 months post-randomisation.

Secondary outcomes

- Change in weight (in kg) at 1, 2, and 6 months post-randomisation.
- Change in BMI at 1, 2, 6 and 12 months post-randomisation. BMI is calculated as weight (in kg) divided by the square of height (in metres). The height measured at screening will be used for each follow-up assessment.
- Change in waist circumference (in cm) at 2, 6 and 12 months post-randomisation.
- Change in systolic blood pressure (mmHg) at 2, 6 and 12 months post-randomisation.
- Change in diastolic blood pressure (mmHg) at 2, 6 and 12 months post-randomisation.
- Change in the Food Craving Inventory score (Frequency domain) at 1, 2, 6, and 12 months post-randomisation.
- Change in the Food Craving Inventory score (Strength domain) at 1, 2, 6, and 12 months post-randomisation.
- Change in Food Knowledge Assessment Questionnaire score at 2, 6, and 12 months post-randomisation.
- Change in the Three Factor Eating Questionnaire score (Cognitive Restraint domain) at 2, 6, and 12 months post-randomisation.
- Change in the Three Factor Eating Questionnaire score (Uncontrolled Eating domain) at 2, 6, and 12 months post-randomisation.
- Change in the Three Factor Eating Questionnaire score (Emotional Eating domain) at 2, 6, and 12 months post-randomisation.
- Change in the International Physical Activity Questionnaire (IPAQ) score (MET-minutes/week domain) at 2, 6, and 12 months post-randomisation.
- Change in the International Physical Activity Questionnaire (IPAQ) score (Sitting domain) at 2, 6, and 12 months post-randomisation.
- Proportion of participants losing 5% of body weight at 2, 6, and 12 months post-randomisation.
- Proportion of participants losing 10% of body weight at 2, 6, and 12 months post-randomisation.

Scoring details for the Food Craving Inventory, the Food Knowledge Assessment Questionnaire, the Three Factor Eating Questionnaire, and the International Physical Activity Questionnaire are available in Appendix 2.

Weight, BMI, waist and blood pressure outcomes were measured by researchers who were blind to treatment arm. These researchers were affiliated with the trial team, but were involved only in collecting outcomes during follow-up, and had no role in providing the intervention, and no contact with patients other than whilst collecting follow-up measurements.

1. **STUDY METHODS**

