**Overall study design and plan**

Target for randomisation: 220 intervention and 110 control participants

Date of first randomisation: 27/09/2012

Date of last randomisation: 30/01/2014

Trial design: Individually randomised, parallel group

Who is blinded: Researchers affiliated with the study team conducting measurements at 6 and 12-month follow-up. Patients and those delivering the intervention are aware of the patient’s treatment allocation.

Randomised Interventions: Intervention (WAP) vs. control (Nurse counselling)

Allocation ratio: 2:1

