**Database**

Description

Data were entered into the online database, ‘Oracle Database version 11’, hosted at the Barts Cancer Centre. The Electronic Data Capture forms are web based and built using Java with data validation in JavaScript (Java framework Struts 2).

Data quality

When recruitment and follow-up are complete, the study team will clean the data in the following way: values for each variable will be sorted, and those at the extremes will be checked to ensure that they are within the expected range.

Source data verification will also be conducted: a random sample of 10% of CRFs will be selected, and a member of QA team (PCTU) will compare all written entries with those entered onto the main study database. The pre-specified data quality target is ≤ 2% discrepancy rate between entries in the CRF and the electronic database. If an error is found in >2% of entries, the quality target for data entry will not have been met, and all CRF data will be cross-checked against data in the study database. (This would be done by counting up the maximum number of data items that could be entered for a patient on each of the CRFs, ignoring free text fields. Errors will be tallied and these would include any items that were inadvertently missed out.)

Derived and computed variables

All derived and computed variables will be documented in the analysis programmes.

1. **GENERAL ISSUES FOR STATISTICAL ANALYSIS**

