*Change in Food Knowledge Assessment at 2, 6 and 12 months*

These outcomes will be analysed using the same method as change in weight at 6 and 12 months. The baseline value of food knowledge will also be as a covariate in the model. Food Knowledge Assessment measurements at 2, 6, and 12 months will be included in the model.

*Change in Three Factor Eating Questionnaire (Cognitive Restraint domain) at 2, 6 and 12 months*

These outcomes will be analysed using the same method as change in weight at 6 and 12 months. The baseline value of the Three Factor Eating Questionnaire (Cognitive Restraint domain) will also be included as a covariate in the model. Cognitive Restraint domain measurements at 2, 6, and 12 months will be included in the model.

*Change in Three Factor Eating Questionnaire (Uncontrolled Eating domain) at 2, 6 and 12 months*

These outcomes will be analysed using the same method as change in weight at 6 and 12 months. The baseline value of the Three Factor Eating Questionnaire (Uncontrolled Eating domain) will also be included as a covariate in the model. Uncontrolled Eating domain measurements at 2, 6, and 12 months will be included in the model.

*Change in Three Factor Eating Questionnaire (Emotional Eating domain) at 2, 6 and 12 months*

These outcomes will be analysed using the same method as change in weight at 6 and 12 months. The baseline value of the Three Factor Eating Questionnaire (Emotional Eating domain) will also be included as a covariate in the model. Emotional Eating domain measurements at 2, 6, and 12 months will be included in the model.

*Change in International Physical Activity Questionnaire (MET-minutes/week domain) at 2, 6 and 12 months*

These outcomes will be analysed using the same method as change in weight at 6 and 12 months. The baseline value of the MET-minutes/week domain will also be included as a covariate in the model. MET-minutes/week domain measurements at 2, 6, and 12 months will be included in the model.

*Change in International Physical Activity Questionnaire (sitting domain) at 2, 6 and 12 months*

These outcomes will be analysed using the same method as change in weight at 6 and 12 months. The baseline value of the sitting domain will also be included as a covariate in the model. Sitting domain measurements at 2, 6, and 12 months will be included in the model.

*Proportion of participants losing 5% of body weight at 2, 6, and 12 months*

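### The IPAQ MET-minutes score has no upper limit or rule for implausible reports, yet its change is compared as a difference in means, so a few records can cost this secondary outcome much of its precision

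*SAP*

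**What the plan says.** The SAP's Outcome measures section lists as a secondary outcome "Change in the International Physical Activity Questionnaire (IPAQ) score (MET-minutes/week domain) at 2, 6, and 12 months post-randomisation". Appendix 2 defines the score as 3.3, 4.0 and 8.0 times the self-reported minutes times days of walking, moderate and vigorous activity, summed. The only bound is at the bottom: the score "is expressed on a continuous scale with a minimum score of 0".

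Under Analysis of secondary outcomes, the score is analysed by the same linear mixed model as weight, and "The baseline value of the MET-minutes/week domain will also be included as a covariate in the model". Table 4 shows the change as mean (SD), and its footnote says "Treatment effects are presented as a difference in means (estimated from a mixed-effects regression model) between the two groups (WAP vs. control) for all outcomes", with only the 5% and 10% weight-loss outcomes excepted. No transformation, median or robust analysis is planned for this score. The sensitivity analyses concern the primary outcome only.

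The Database section offers three safeguards. The electronic forms have built-in validation, whose limits are not given. Values are sorted and "those at the extremes will be checked to ensure that they are within the expected range". A 10% sample of CRFs is compared with the database.

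**The concern.** The formula multiplies a self-report by up to 8.0 and then by days, so one careless or misunderstood answer can yield a score far above anything plausible. As written, the three activities may even total more than 24 hours a day. The other questionnaire scores whose ranges Appendix 2 fixes cannot do this: Food Knowledge runs 0–10, each Food Craving domain 0–25, and the Three Factor Eating domains are means of items scored 1–4.

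The safeguards do not close the gap. The extremes check has no stated range for this score and no action for a value that fails. The CRF comparison passes an implausible answer that was entered faithfully. Two analysts following the SAP could treat the same record differently and report different effects. Exercise and pedometer targets are part of the WAP content, so a noisy activity result would be a real loss.

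**Working it through.** **Inputs from the SAP.** The score weights are 3.3, 4.0 and 8.0 (Appendix 2). Arm sizes come from "Target for randomisation: 220 intervention and 110 control participants". Sample size determination assumes 50% follow-up at one year, giving 55 control and 110 WAP.

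**The plan's own figures.** The SAP states no expected effect or SD for IPAQ. The sample size that sets the arms does reproduce. For a 1.3 kg difference, SD 3, 5% two-sided and 90% power, n = 112 per group. The design effect is 1 + 17 × 0.05 = 1.85, and 112 × 1.85 = 207.2, rounded up to 208. Power at 108:216 is 90.1%.

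**Upper end of the formula.** Vigorous activity alone allows 8 × 1,440 × 7 = 80,640. All three activities at 24 hours would give 15.3 × 1,440 × 7 = 154,224.

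**Shift in an arm mean from one record.** Score = 8 × minutes × 7; shift = score / number analysed.

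| Vigorous activity, 7 days | Score | n = 55 | n = 110 | n = 220 |
|---|---|---|---|---|
| 4 h/day | 13,440 | 244 | 122 | 61 |
| 8 h/day | 26,880 | 489 | 244 | 122 |
| 12 h/day | 40,320 | 733 | 367 | 183 |
| 16 h/day | 53,760 | 977 | 489 | 244 |

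Control corresponds to n = 55 (50% follow-up) or 110 (full); WAP to n = 110 or 220. If the participant's true score were an assumed 2,000, the 489 becomes (26,880 − 2,000)/55 = 452.

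**Scale for comparison (assumed).** Walking 30 more minutes on 5 days is 3.3 × 30 × 5 = 495. The range is 165 (10 minutes on 5 days) to 693 (30 minutes on 7 days).

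**Baseline adjustment.** In 1,000 simulated baseline-adjusted change regressions on assumed log-normal data (55 v 110), a simplified stand-in for the SAP's model, one control record of 26,880 moved the difference by about −457 and raised its standard error from 204 to 381.

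**Equal over-reporting in both arms.** If a fraction p of records carries excess E, each arm mean rises by pE whatever its size, so the expected difference is unchanged. The variance is not. The added standard deviation of the difference is E × √[p(1 − p)(1/55 + 1/110)]. With p = 1% (assumed) this is 0.01643 × E.

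- Uncapped, E = 24,880: 409. Combined with 204: √(204² + 409²) = 457.
- Score held at 10,080 (vigorous activity limited to an assumed 180 minutes a day, 8 × 180 × 7), E = 8,080: 133. Combined: √(204² + 133²) = 244.

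A separate simulation on assumed log-normal data, with a true effect of 500 and 1% of records at 26,880, agrees in direction. Truncating the score at 10,080 cut the spread of the estimate from 630 to 354 and raised power from 13% to 27%. Part of that gain comes from trimming the assumed distribution's own long tail.

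**The case against.** The strongest reply has four parts.

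- **Safeguards exist.** Form validation may already restrict minutes or days, and a score of 26,880 would probably be flagged by the extremes check. This stands in part: the gap is the missing IPAQ range and the missing handling rule, not a total absence of checks.
- **The outcome is a change score.** It can be negative and is adjusted for baseline, and the SAP gives no IPAQ distribution, so skewness is an assumption. This stands, but neither feature removes a single record's leverage, as the baseline-adjusted simulation shows.
- **The example is extreme.** The 489 counts the whole score as excess and uses the 50% follow-up that the SAP itself calls conservative. This stands, which is why the table shows the range. In WAP at full follow-up, the same record moves the mean by only 122.
- **Errors cancel.** A reader might infer that over-reporters will produce a false activity effect, chiefly through the smaller control arm. The SAP does not support that. WAP has twice the records, each with half the leverage. In 3,000 simulated trials on assumed log-normal data with 0% to 5% of all participants reporting 26,880, the mean effect stayed near zero and false positives were 4.3–4.9%. Only forcing exactly one such record into control raised this, to 8.9%. An outlier also inflates the standard error. Cancellation does require equal rates in the two arms, and the SAP gives no reporting rates by arm.

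The scope is also limited: this is one of many secondary outcomes, and it is not among those to be graphed.

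**Conclusion.** The point holds as a weakness of precision. Following the SAP as written admits scores up to 80,640 from vigorous activity alone into a comparison of means, with no rule for a correctly recorded but implausible value. One record of 26,880 moves a control mean by about 489 at 55 followed up (244 at 110) and a WAP mean by about 244 at 110 (122 at 220). If 1% of records were like this in both arms, the standard error would roughly double in the worked case (204 to 457), and truncation would recover most of the loss (244). In any one trial the estimate could be distorted by chance in either direction.

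These sizes rest on assumptions that the SAP does not supply: the spread of IPAQ scores, the frequency and size of implausible reports, and what counts as a real activity effect. If there were no such reports, little would be lost. The conclusion does not extend to a systematic false effect, nor to the primary weight analysis, which does not use this score. The change is worth making because it is cheap and is only credible if fixed before unblinding.

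**What to change.** Add to the MET-minutes scoring rule in Appendix 2, before unblinding and identically for both arms and every visit including baseline:

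- A stated numeric truncation limit on daily minutes in each activity. An illustrative limit is 180 minutes, an assumption for the sponsor to confirm. The highest possible score would then be 15.3 × 180 × 7 = 19,278, which moves the control mean by at most about 350 at n = 55 and the WAP mean by about 175 at n = 110. A vigorous-only record at the limit (10,080) would move them by 183 and 92.
- A stated action for records whose reported activities, before truncation, sum to an impossible daily total (more than 24 × 60 = 1,440 minutes, or a lower threshold that the sponsor justifies).

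Summarise the score as median (IQR) alongside the mean. Keep the stated mixed model, on the truncated score, as the main analysis. Add the untruncated score and a transformed or robust analysis as sensitivity analyses. A log(score + 1) model is better kept there than made primary, because it is very sensitive to movement away from zero.

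The cost is a few lines of SAP text and derivation code. Truncation slightly understates genuinely very active participants. It is preferable to exclusion where possible: a baseline value set to missing would be mean-imputed under General analysis principles, and removing high follow-up values makes missingness depend on the value itself, which strains the missing-at-random assumption.
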